### Participants

The study will aim to recruit 40 participants, 20 participants in each arm. All participants will be aged between 16-75, living in London, and have symptoms of Depersonalisation and/or Derealisation currently meeting DSM-V (1) criteria for DDD. This will be assessed by the research assistant (RA) in their initial (T0) screening interview by asking the participant the following two questions, which make up part of the diagnostic criteria in the DSM-V (1) :

“Over the last two weeks, how often have you had:

1. Experiences of unreality, detachment, or being an outside observer with respect to one's thoughts, feelings, sensations, body, or actions (e.g., perceptual alterations, distorted sense of time, unreal or absent self, emotional and/or physical numbing). [Depersonalisation]

0 =not at all; 1=several days; 2=more than half the days; 3=nearly every day”

1. Experiences of unreality or detachment with respect to surroundings (e.g., individuals or objects are experienced as unreal, dreamlike, foggy, lifeless, or visually distorted). [Derealisation]

0=not at all; 1=several days; 2=more than half the days; 3=nearly every day.”

The total score will be calculated as follows:

1. Total score = (a + b).
   1. Scores <3 = mild-moderate DDD.
   2. Scores >=3 = moderate-severe DDD.

Other DSM-V criteria will be assessed including intact reality testing, that the symptoms result in significant distress and/or functional impairment, and that the DDD symptoms cannot be better explained by another condition. Participants will be excluded if they have any of the following co-morbid diagnoses: any psychosis spectrum disorder, substance dependence, intellectual disability, Post Traumatic Stress Disorder (PTSD), or cognitive impairment due to head injury or organic disorder. Comorbidity with anxiety and/or depressive disorders will not be an exclusion criterion.

Additionally, participants will be excluded from the study if they have previously received CBT specifically for the treatment of DDD; have a score below clinical severity (i.e. total score < 3) on the diagnostic questions; cannot provide informed consent; do not have sufficient proficiency in English to engage in CBT; require special communication needs arrangements; are not registered with a GP practice or are involved in any other mental or physical research studies (including drug trials).

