**Diversity and Inclusion.** To increase the likelihood that the study sources a representative sample, recruitment will take place across two London mental health trusts covering six boroughs. Camden and Islington NHS Foundation Trust (C&I) is an inner London trust which had over 45,600 service users in 2020 (18). The trust covers the boroughs of Camden, Islington, and Kingston. Islington is the most densely populated local authority area in England and Wales and is among the poorest 20% of neighbourhoods in England (19). Barnet, Enfield and Haringey NHS Foundation Trust (BEH) is an outer London trust which had 146,000 service users in 2022 (20). Approximately a third of individuals across all six boroughs are residents from black, Asian or minority ethnic groups (19, 21–25). We will be recruiting from primary, secondary and tertiary care services across these Trusts.

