### Sample Size

There is no formal sample size calculation, or priori power calculation. Instead, a minimum of 24 participants, 12 in each arm, has been suggested for pilot studies (26). This minimum recruitment strategy requires recruiting 29 eligible participants in total (encompassing a nominal 20% dropout rate). This study aims to recruit 20 participants in each arm who complete. We believe this number will give us a final sample large (and sufficiently diverse) enough to assess the practicalities of recruitment, retention, randomisation, and intervention delivery, as well as to obtain the necessary data for the statistical inferences required.

A previous naturalistic self-controlled cross-over study found the effect size between the treatment period and the waiting period to be 0.52 (improvement in favour of treatment). This translated into a decrease of 36 points on the CDS Scale. Using this change score, a correlation of 0.9 which was observed for intra-participant correlation, and the standard deviation of the CDS at each phase of the crossover study, we anticipated that the required sample size would be 29 participants per arm (using the ANCOVA method). Our planned recruitment of 20 per arm provides sufficient power to provide information on the magnitude, direction, and precision of the treatment effect from the feasibility study to power (with sufficient precision) a subsequent definitive RCT if appropriate (15).

To meet our relatively conservative aim of 20 participants completing the trial in each arm we will need a recruitment rate of 5-10 participants a month during the 6-month recruitment period. Historical data demonstrates a referral rate of one referral per week, which would be adequate for the proposed sample size.

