### Data Collection

This study will focus on assessing the feasibility of future studies and the acceptability of CBT-f-DDD as an intervention (see Appendix A). To assess feasibility, resources needed to complete the feasibility trial will be recorded including:

- Length of time required for RA to complete assessments and to collect and analyse data, collected from RA time sheets.
- CBT attendance rate, collected from electronic patient records.
- The amount and nature of supervision required, collected from supervision notes.

Recruitment data collected throughout the study will also aid in assessing the feasibility:

- Number of referrals from each source.
- Number of ineligible referrals.
- Reasons for ineligibility.
- Rates and reasons for refusal to be included in the study.
- Rates of attrition.
- Reasons for withdrawing from the study.

We will measure the participants’ acceptability of the intervention and study procedure, and the therapists’ acceptability of the intervention. Attrition rates, and the number of therapy dropouts will also be collected in the measurement of acceptability.

Participants’ acceptability of the intervention as well as the assessment procedures and measures will be collected through an end of intervention questionnaire at T2 and semi-structured qualitative interviews at T3 carried out by RAs. Participants’ acceptability of CBT-f-DDD will be measured through questions regarding which aspects of the treatment they found helpful and unhelpful, their perceived impact of the intervention, and their satisfaction with the intervention and therapists. Additionally, a global measure of change question with a binary response will be asked:

*“Do you feel better? Yes/No”*

Therapists’ acceptability of the intervention will be measured through semi-structured qualitative interviews at T2. This will measure therapist satisfaction with training and supervision, their confidence in delivering the therapy, their views of the intervention’s value, and the perceived impact and feasibility of delivery in standard clinical settings. The therapists’ adherence to the intervention protocol will also be examined in measuring the acceptability of the intervention through:

- Participant’s engagement with CBT-f-DDD and homework tasks using a Likert scale for clinicians to complete,

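### The historical rate of one referral a week is called adequate, but as written it gives about 26 referrals in 6 months, below the protocol's own 5 a month, 29 and 40

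*Protocol*

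**What the plan says.** The Participants section sets the target: "The study will aim to recruit 40 participants, 20 participants in each arm". The Sample Size section words it as completers: "This study aims to recruit 20 participants in each arm who complete". The two are the same only if nobody drops out.

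The Sample Size section also gives a floor. It notes that "a minimum of 24 participants, 12 in each arm, has been suggested for pilot studies", and then that "This minimum recruitment strategy requires recruiting 29 eligible participants in total (encompassing a nominal 20% dropout rate").

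Its last paragraph makes two statements in succession. To reach 20 completers per arm, "we will need a recruitment rate of 5-10 participants a month during the 6-month recruitment period". Then: "Historical data demonstrates a referral rate of one referral per week, which would be adequate for the proposed sample size".

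Three other places bear on how many referrals become participants:

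- Participants lists a long set of exclusions, and its diversity paragraph says that "recruitment will take place across two London mental health trusts covering six boroughs".
- Data Collection and Analyses plan to record losses before randomisation, among them "Number of ineligible referrals" and rates of refusal.
- Procedure adds self-referral through the trust and charity websites, with no expected number.

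**The concern.** The two consecutive sentences do not agree. The first gives a monthly rate that the trial needs. The second offers a weekly rate as sufficient, and that weekly rate, put on a monthly scale, is below the bottom of the range just given. The comparison also favours the plan, because it sets referrals against participants as if none were ineligible and none refused.

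The ability to recruit is the first aim of the study, and the historical rate is the only basis that the protocol states for expecting to reach its target. If that basis does not support the target, a shortfall against 40 could not be read properly: it might show a difficulty with the trial, or only the referral volume that the protocol's own figure implied.

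**Working it through.** **Inputs, all from the protocol.** Target 40, minimum to recruit 29, minimum evaluable 24, dropout 20%, required rate 5 to 10 a month, recruitment period 6 months, historical rate one referral a week (Sample Size and Participants). Two recruiting trusts (Participants, Procedure). No conversion rate from referral to randomisation is given, so any below 100% used here is an assumption.

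**1. The plan's own minimum.** 24 × 1.2 = 28.8, rounded up to 29. This reproduces the stated figure. Dividing by (1 − 0.2) gives 24 / 0.8 = 30. The same two rules applied to 40 completers give 40 × 1.2 = 48 and 40 / 0.8 = 50.

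**2. What the historical rate yields, read as an overall rate.** 1 × 26 weeks = 26 referrals; 52 / 12 = 4.3 a month. Taking a month as 4 weeks gives 24.

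**3. Comparison at 100% conversion.**

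| Number to recruit | Needed a month (n / 6) | 26 as a share | Referrals a week needed (n / 26) | Months at one a week |
|---|---|---|---|---|
| 29 (stated minimum) | 4.8 | 90% | 1.1 | 6.7 |
| 40 (target recruited) | 6.7 | 65% | 1.5 | 9.2 |
| 48 (40 completers, × 1.2) | 8.0 | 54% | 1.8 | 11.1 |
| 50 (40 completers, / 0.8) | 8.3 | 52% | 1.9 | 11.5 |

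The stated word, adequate, is not reproduced for any row. 26 exceeds only the 24 evaluable participants, and then only with no ineligibility, refusal or dropout.

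**4. The required range.** 5 × 6 = 30 and 10 × 6 = 60. The range contains 40, 48 and 50, but its lower end does not reach any of them.

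**5. Chance variation.** If referrals are Poisson with mean 26 and all are randomised (assumptions), P(at least 29) = 30% and P(at least 40) = 0.6%.

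**6. The rate read as per trust.** 2 × 26 = 52 referrals. Conversion needed:

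- 29 recruits: 29 / 52 = 56%
- 40 recruits: 40 / 52 = 77%
- 48 recruits: 48 / 52 = 92%
- 50 recruits: 50 / 52 = 96%

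With Poisson mean 52 and full conversion, P(at least 40) = 96%. At an assumed 70% conversion the mean is 36.4 and P(at least 40) is about 30%.

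**7. Effect of conversion on the referrals needed.** For 40 recruits in 26 weeks: 1.54 / 0.7 = 2.2 a week, or 1.54 / 0.5 = 3.1 a week. For 48 to 50: 2.6 to 2.7 a week at 70%, and 3.7 to 3.8 at 50%. These two conversion rates are illustrative and have no source in the protocol.

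**The case against.** **The unit of the rate is not stated.** This is the strongest reply, and it stands as a limit on certainty. Recruitment runs across two trusts and several levels of care, and one a week might mean one per trust. The figures of 26, 30% and 0.6% all depend on the overall reading. But the text does not say per trust, and on that reading the sentence still lacks the conversion rate that would make it true: 77% for 40 recruits, and 92 to 96% for 40 completers.

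**Other routes add referrals.** Self-referral and wider identification by clinicians may well do so. No number is attached to them, and the sentence rests adequacy on historical data alone.

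**The range of 5 to 10 contains what is needed.** This is true. The range is imprecise rather than false; the fault lies in the sentence that follows it.

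**Recruitment is what a feasibility study is there to find out.** This is also true, and it limits the severity. A reader might infer that the historical rate acts as a feasibility benchmark, so that a shortfall would by itself lead to the conclusion that a definitive trial is infeasible. The protocol does not support that. It sets no recruitment threshold or stop/go rule, its Analyses section treats recruitment as parameters to be examined, and recording referrals by source would help to show whether low volume was the cause.

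A reader might also infer that the trial must end below 12 per arm. At an assumed 50 to 70% conversion of 26 referrals, 13 to 18 would be randomised, but that conversion rate is not in the protocol and the result cannot be stated as a finding.

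**Conclusion.** The statement of adequacy is wrong as written. Read plainly, one referral a week gives about 26 referrals in 6 months, or 4.3 a month. That is 3 short of the protocol's minimum of 29 and 14 short of its target of 40, before any of the losses that it plans to record. Read per trust, adequacy is possible for 40 recruits but not shown, and it is very tight for 40 completers. No other section reconciles the two sentences.

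The conclusion assumes a 26-week period and a constant rate; the shortfall on the plain reading does not depend on any conversion assumption, since it is present at 100%. The consequence is one of interpretation: a shortfall against 40 should be read in the light of the referral volume expected. Randomisation, outcomes, analysis and safety provisions are not affected. Severity: should-fix.

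**What to change.** In the last paragraph of Sample Size:

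1. Delete the unqualified statement that the historical rate is adequate.
2. State the source of the rate and its unit (overall, per trust or per service). If it is overall, say that it yields about 26 referrals in 6 months and is not sufficient alone.
3. Replace the 5 to 10 range, whose lower end gives only 30, with the required rate: 6.7 randomised a month for 40 recruited, or 8.0 to 8.3 a month for 40 completers (48 by the × 1.2 rule that gives the protocol's 29, 50 by dividing by 0.8). Say which target applies and use one dropout rule throughout.
4. State an assumed conversion from referral to randomisation and the weekly referrals that it implies. The lower bounds at 100% conversion are 1.5 a week for 40 and 1.8 to 1.9 for 48 to 50. Give any expected contribution from self-referral separately.
5. Align either the recruitment period or the number expected in 6 months with those figures.

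The cost is wording and a less favourable stated figure. A longer recruitment period is needed only if the sponsor chooses that option over a smaller expected number.

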### Intervention

CBT for DDD aims to reduce distress associated with DDD symptoms by changing catastrophic attributions through general and personalised psychoeducation; developing a shared formulation of difficulties by linking DDD symptoms to anxiety, mood, and/or past traumas; enhancing coping strategies; and by using cognitive restructuring techniques to modify unhelpful appraisals. CBT-f-DDD theorises that DDD symptoms are reduced by altering the maintenance cycle and associated distress.

The intervention will be delivered in addition to the participant’s TAU over a six-month period. The CBT-f-DDD protocol and training manual developed by ECMH will be provided to therapists during training, and each therapist will adjust these as appropriately determined to the individual needs of the client. The intervention comprises the following components (see Table 1).

**Table 1.** CBT-f-DDD intervention components

| **Engagement and psychoeducation about DDD** |
| --- |
| - Managing expectations and goal setting |
| - General and individualised psychoeducation about DDD |
| **Developing the shared formulation** |
| - Diary keeping and analysis |
| - Identifying external and/or internal triggers |
| - CBT vicious cycle of recent, typical incident |
| **Cognitive strategies: content and process** |
| - Restructuring beliefs about DDD |
| - Recognising thinking biases |
| - Working with cognitive processes to reduce rumination, worry and hypervigilance |
| **Emotional regulation strategies** |
| - Anxiety and mood management strategies |
| - Grounding strategies |
| **Behavioural Interventions** |
| - Psychoeducation about safety seeking behaviours |
| - Behavioural activation |
| - Behavioural experiments - Graded exposure |
| **Working with common co-morbid conditions triggering DDD** |
| - Anxiety disorders, low mood, low self-esteem |
| - Working with negative core beliefs/schemas, procrastination, perfectionism |
| - Substance use |
| **Working with Issues Related to Onset** |
| - Trauma-focused CBT imaginal exposure |
| - Dealing with physical reminders of onset |
| - Chair work where the client uses different chairs to represent different aspects of themselves to foster communication and insights from taking various perspectives |
| **Working with Predisposing Factors** |
| - Working with past trauma or life adversity |
| **Staying Well Plans** |

### Treatment as Usual Condition

For some participants, the TAU will involve contact with a therapist through their mental health team or medication prescribed by their GP and/or mental health team. The TAU will vary from individual to individual but may consist of waitlist, short-term psychological therapies, or prescription of antidepressants such as SSRIs. Participants will be asked to keep a record of the type and frequency of their appointments with clinical services and treatments offered. These data will be supplemented with information provided by their key worker or through clinical note screening.

### Procedure

**Phase 1: Recruitment and Training*.*** Participants and therapists will be recruited via two NHS Mental Health Trusts:

- An inner London mental health trust (Camden and Islington NHS Foundation Trust (C&I))
- An outer London mental health trust (Barnet, Enfield, and Haringey Mental Health NHS Trust (BEH))

The two NHS Trusts will be our primary recruitment sites, and clinicians will be aiding in identification and recruitment as well as becoming the first point of contact for potential participants. Additionally, the study will be advertised on both Trust’s websites as well as on the Unreal Charity’s website (<https://www.unrealuk.org/>) (27), which provides a route to self-refer to the study.

**Figure 1.** Trial Flowchart

If self-referred, the potential participant will be provided with a Participant Information Sheet (PIS) and follow the route to obtaining informed consent (unless they satisfy the exclusion criteria or do not fulfil the inclusion criteria). No information about participants will be collected and no research activities will be held within Unreal. Unreal (27) will be used solely as a participant identification centre whereby the participants recruited will be advised that they will be referred to one of the NHS trusts for the duration of their participation in the study. We will involve the externally recruited participants’ GPs/mental health teams to gain information relevant to risk, current prescribed medication, and use of services.

Informed consent will be collected at T0 by aRA, prior to baseline interview and after the eligibility screening. Participants will be randomised following the baseline interview (T0) and collection of baseline data (see Figure 1).

**Training of Therapists.** Training of therapists will take place in half-day workshops. All therapists involved will be qualified and have experience with CBT. We will collect data about whether therapists included in the study are accredited with the British Association of Behavioural and Cognitive Psychotherapists (BABCP) and their past qualifications and years of experience with CBT. The training workshops will aim to help therapists understand DDD and demonstrate the adaptation of existing CBT skills to work with DDD using clinical case examples. All therapists will receive a hard copy of the training manual with additional materials and reading. As this is a feasibility study, we will also be examining whether a half-day training would be sufficient to supply these skills and knowledge.

There is an agreement with the relevant C&I and BEH Heads of Services that therapists across the trusts will attend the training in order to be able to take on one or more cases of DDD clients. We envisage having a relatively large number of therapists with a small trial caseload to reduce the burden on services and to maximise the number of therapists who will benefit from training and specialist supervision.

**Phase 2: Treatment Phase***.* Prior to commencing therapy and one month after randomisation, the participants in both arms will be assessed again (T1). Those in the intervention arm will receive a minimum of 12 (maximum of 24) 1-hour-long CBT-f-DDD sessions. The location of these sessions will depend on participant and/or therapist preference and can be conducted face-to-face or via videoconferencing. Meta-analyses comparing the efficacy of psychological therapies conducted face-to-face versus through videoconferencing has shown similar symptomatic improvement and client satisfaction scores across conditions (28, 29). Additionally, a recent RCT examining online versus in-person CBT for anxiety conditions did not find a significant difference in outcome measures between treatment conditions (30). It is not expected that this study will find any differences between the two conditions but will collect the modality used for monitoring purposes. The CI [ECMH] will provide fortnightly group specialist supervision to therapists delivering the intervention. For those in the TAU arm, there will be a record kept of the type and frequency of their appointments with clinical services and the treatments offered.

At the end of the intervention period, all participants will complete an end of treatment assessment (T2). Therapists will also be invited to participate in a semi-structured qualitative interview to explore their views on the acceptability, feasibility and perceived impact of training, therapy delivery and supervision once they have completed work with all their clients (T2).

**Phase 3: Follow-up*.*** The follow-up period will begin nine months after randomisation and three months after the intervention ended. Participants from both arms of the trial will be invited to the follow-up assessment (T3). For those in the intervention arm, the follow-up will additionally involve a semi-structured qualitative interview to record their experiences of treatment and its impact. We will attempt to contact those who were lost to follow-up to try to understand their reasons for dropping out. Particularly, we are interested in whether the loss of contact is related to intervention acceptability issues. Upon completion of their participation in the study, participants will receive a £10 Love2Shop voucher.

Dissemination of the findings will take place within Unreal, NHS partners, University College London (UCL), and the wider academic/CBT community. This will be achieved through conference presentations, and written peer-reviewed publications. Participants will have the option of requesting study results upon completion by ticking a box in the consent form. Unreal as a co-applicant on this study will assist the dissemination of materials to the lay public across various platforms. There will be a plain English summary published on the charity website and the results of the study will be included in their charity newsletter which is circulated to 1100 recipients (31). Additionally, a plain English thread will be posted on their X account to reach both wider academic audiences and clinical populations.

